### Outcome definitions

2.9

#### Primary outcome

2.9.1

The primary outcome of this study is PFS, defined as the time from treatment initiation to first radiological disease progression according to the Response Evaluation Criteria in Solid Tumors version 1.1 (RECIST v1.1) or death, whichever occurs first. The radiologic evaluation will be performed every 12 weeks (± 7 days) by unblinded investigators and centrally by an independent group of radiology experts, beginning after treatment initiation.

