### Randomization and blinding

2.4

All included patients will be randomized into intervention, control, and standardized treatment groups in a 3:3:2 ratio using a computer-generated random sequence by a clinical research assistant. This study is an open-label trial, so participants, care providers, and investigators will not be blinded.

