### Interventions

2.5

The study flow is presented in **Figure 1**. Patients in the intervention group will be given sintilimab (200 mg, IV, D1, once every 3 weeks) plus fruquintinib (5 mg, po, D1-14, once every 3 weeks) in combination with liver-directed radiotherapy. A 21-day treatment cycle of sintilimab (200 mg, IV, D1, once every 3 weeks) will be given intravenously on day 1 of each cycle, and fruquintinib will be given on days 1 through 14 of each cycle. The radiologist will determine the radiation division pattern based on the location and volume of the liver metastases. For liver oligometastases, stereotactic body radiation therapy (SBRT) will be performed with a dose of 40–50 Gy/5 F, 60–70 Gy/10 F, or 65 Gy/13 F. For multiple liver metastases, SBRT plus low-dose radiation therapy (LDRT) will be performed. The appropriate lesions will be selected to receive SBRT with a dose of 40–50 Gy/5 F, 60–70 Gy/10 F, or 65 Gy/13 F, and the remaining liver lesions will undergo LDRT at a total dose of 1–10 Gy with 0.5-2.0 Gy/F. One or more appropriate lesions will be selected by the physician based on the surrounding organs at risk. Extrahepatic lesions will not receive radiation therapy. Liver radiotherapy will be administered within 1 week of initiating immunotherapy. For patients receiving a 5-fraction regimen, the volume receiving ≥15 Gy will be limited to <700 cc and the Dmean will be <16 Gy. For those treated with 10 or 13 fractions, the volume receiving ≥24 Gy will be limited to <700 cc and Dmean will be <24 Gy for patients with Child-Pugh class A, and the limits will be V18Gy <700 cc and Dmean <18 Gy for patients with Child-Pugh class B. **Figure 2** shows an example of target area delineation and radiation dose distribution for two patients.

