#### Tumor imaging during the study

2.7.2

Tumor imaging will be evaluated every 12 weeks (± 7 days) starting from the first dose. Unscheduled imaging evaluations will be conducted at any time if the subject experiences clinical disease instability during the study.

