#### Secondary outcomes

2.9.2

Objective response rate (ORR), defined as the proportion of subjects with a CR or PR by RECIST v1.1;Disease control rate (DCR), defined as the proportion of subjects with a CR, PR, or SD by RECIST v1.1;Overall survival (OS), defined as the time from treatment initiation to death from any cause;The incidence, severity, and association of any AEs with study drugs, treatment-emergent adverse events (TEAEs), SAEs, and immune-related adverse events (irAEs).

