#### Statistical analysis methods

2.13.2

Clinical characteristics and safety outcomes will be summarized using descriptive statistics. Unless otherwise stated, continuous data will be statistically described using mean (± standard deviation) or median (minimum, maximum). Categorical data will be statistically described using frequencies (percentages). Cox proportional hazard models will be used for univariate and multivariate survival analyses, with HRs and 95% confidence intervals (CIs) calculated. Subgroup analyses will be conducted by the characteristics of patients and liver metastases (liver oligometastases or multiple liver metastases). Both the intention-to-treat (ITT) population and the per-protocol population will be used for efficacy and safety analyses. The worst-case imputation and complete-case analysis will be performed as sensitivity analyses to handle the missing data and dropouts (24). The SAS 9.2 (or higher) will be used for statistical analyses, using a one-sided 0.05 hypothesis test of superiority, and 95% CIs and *P* values will be reported for group comparisons.

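### PFS and OS run from treatment initiation, so a patient randomised but never treated has no defined survival time in the ITT analysis

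*Protocol article*

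**What the plan says.** The protocol article, section 2.9.1 (Primary outcome), states: "The primary outcome of this study is PFS, defined as the time from treatment initiation to first radiological disease progression", with death as the alternative event. Section 2.9.2 (Secondary outcomes) uses the same origin: "Overall survival (OS), defined as the time from treatment initiation to death from any cause". The article does not define treatment initiation further, and it nowhere gives randomisation as a time origin.

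Section 2.13.2 (Statistical analysis methods) sets the analysis populations: "Both the intention-to-treat (ITT) population and the per-protocol population will be used for efficacy and safety analyses". Section 2.4 (Randomization and blinding) has patients "randomized into intervention, control, and standardized treatment groups in a 3:3:2 ratio" and adds: "This study is an open-label trial, so participants, care providers, and investigators will not be blinded".

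The imaging clock in section 2.7.2 also starts at treatment: "Tumor imaging will be evaluated every 12 weeks (± 7 days) starting from the first dose". Section 2.13.1 makes intervention versus control the primary analysis, with 24 and 23 patients.

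**The concern.** An ITT analysis keeps every randomised patient in the arm to which he or she was assigned. That requires an endpoint that exists for every randomised patient. An origin at treatment initiation gives no time zero to someone who is randomised and then declines, deteriorates or dies before the first dose. The endpoint definition and the named population do not fit together for such a patient.

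Open allocation makes this more than a formality. Patients and physicians know the arm before treatment starts, and the two arms of the primary comparison differ by a course of liver radiotherapy. The decision not to start can therefore depend on the arm and on prognosis. Leaving such patients out is a selection made after randomisation, and it weakens the protection that randomisation gives the primary hazard ratio. With 47 patients, a few exclusions could matter.

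**Working it through.** **1. Follow one patient through the text.** Take a patient randomised to either arm of the primary comparison who never receives a dose.

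- Population (2.13.2): the patient belongs to the ITT population, which is used for efficacy.
- PFS (2.9.1) and OS (2.9.2): both start at treatment initiation. This patient has no such date, so neither time is defined.
- Imaging (2.7.1, 2.7.2): the baseline window and the on-study scans are both counted from the first dose, so they supply no alternative origin.
- Follow-up (2.6, 2.12): safety follow-up is counted from the last dose, and survival follow-up comes after it. Survival data are still collected after withdrawal, so a date of death may exist, but there is no date to count from.
- Sensitivity analyses (2.13.2): a complete-case analysis would drop the patient. Worst-case imputation can supply an outcome, but it still needs a time origin.

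No section closes the gap. An analysis plan that is not shown could close it only by overriding the stated endpoint definition.

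**2. Can the start differ by arm?** Sections 2.5 and its continuation after Figure 2 start fruquintinib on day 1 in all three arms, and sintilimab on day 1 in both arms of the primary comparison. Only the intervention arm has a radiotherapy requirement: "Liver radiotherapy will be administered within 1 week of initiating immunotherapy". The Discussion places radiotherapy in the week after immunotherapy starts. Drug start might in practice be held for radiotherapy planning, but no section says so or gives an interval from randomisation to first dose.

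**3. Scale.** Inputs from 2.13.1: 24 + 23 = 47 patients, HR 0.5, one-sided alpha 0.05, medians 1.8 and 3.7 months, 18 months of enrolment, 12 months of follow-up. The number of non-starters is an assumption.

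- Share per non-starter: 1/47 = 2.1%.
- Event probability with uniform accrual R = 18, follow-up F = 12 and λ = ln 2/median: 1 − [exp(−λF) − exp(−λ(F+R))]/(λR). This gives 0.999 (control) and 0.970 (intervention), mean 0.984.
- Schoenfeld power with D events: Φ(√(D/4) × |ln 0.5| − 1.645).

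| Non-starters lost (assumed) | Patients | Expected events | Power at HR 0.5 |
|---|---|---|---|
| 0 | 47 | 46.3 | 76.2% |
| 1 | 46 | 45.3 | 75.4% |
| 4 | 43 | 42.3 | 72.9% |

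The first row is below the planned 80% because this formula needs 52 events at HR 0.5. That is a separate matter, on which this point does not rest. Moving the origin to randomisation leaves the event formula unchanged.

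**The case against.** The strongest reply is that the problem may never arise. The document gives no rate of non-starters, does not say that untreated patients will be excluded, names ITT explicitly, and adds worst-case imputation for dropouts. On the assumed range of 1 to 4 losses, power falls by 0.8 to 3.3 percentage points, which is modest. All of that stands as a limit on size. It does not repair the definition, because an ITT patient without a start date still has no PFS or OS.

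Two stronger readings are tempting and are not supported.

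- A reader might infer that time zero is arm-dependent. The text describes the same day-1 drug start in every arm, and the Discussion puts radiotherapy after immunotherapy has begun. On that reading, radiotherapy planning need not delay time zero. A difference between arms is a possibility, not something the document shows.
- A reader might convert a delay into lost events. At the 1.8-month control median, 1 − exp(−ln 2/1.8 × months) gives 8.5% progressing or dying in one week (0.23 months) and 16.2% in two weeks (0.46 months). The delays are assumed, and the figures do not count lost events. In a patient who then starts treatment, silent progression before the first dose would normally be found at the first on-treatment scan and counted. The patients at risk of being lost are those who never start.

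It is also fair to say that the present scans and endpoint share the first-dose clock and are therefore aligned across arms. The scan timing is not a separate defect; it needs attention only if the origin moves.

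**Conclusion.** The point holds as a mismatch between the endpoint definition and the analysis population. PFS and OS are undefined for a randomised patient who is never treated, and applying the definition literally would remove that patient from the primary comparison after open allocation. This follows from explicit text in sections 2.4, 2.9.1, 2.9.2 and 2.13.2, not from detail that an article leaves to a fuller document.

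The size is open. Each non-starter is about 2% of the primary comparison, but their number and their distribution between arms are not given, so neither the size nor the direction of bias in the hazard ratio can be computed. Possible selection is the main concern, and the loss of power is secondary. It would go too far to conclude that the ITT analysis has already become an analysis of treated patients. The document leaves the two unreconciled and does not state an exclusion.

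**What to change.** Define PFS and OS from the date of randomisation for all randomised patients in the ITT analysis. Keep time from treatment start as a sensitivity analysis.

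If the origin is moved, preferably time the response scans from randomisation in all arms. Otherwise an arm that starts later would have its progressions detected later on the new clock.

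The cost is low. The origin itself changes in two definitions (2.9.1 and 2.9.2), and the sample-size formula is unaffected. Re-anchoring the scans goes further: section 2.7.2, the imaging sentence in 2.9.1 and the assessment schedule (Supplementary Table 1, not shown) would need amending. This is a small downside. The fix assumes that the date of randomisation is recorded for every patient, which is likely but not stated. It should be made before outcome data are examined, since a later change of origin in an open-label trial could look data-driven.

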#### Secondary outcomes

2.9.2

Objective response rate (ORR), defined as the proportion of subjects with a CR or PR by RECIST v1.1;Disease control rate (DCR), defined as the proportion of subjects with a CR, PR, or SD by RECIST v1.1;Overall survival (OS), defined as the time from treatment initiation to death from any cause;The incidence, severity, and association of any AEs with study drugs, treatment-emergent adverse events (TEAEs), SAEs, and immune-related adverse events (irAEs).

### Exploratory analyses

2.10

To explore biomarkers that can predict efficacy, we will collect biological samples, including 10–20 ml of blood, 10–20 ml of stool samples, and 10–20 tumor tissue sections, to support the analysis of cellular components. Biomarkers tested will include but are not limited to: tumor microenvironment, tumor mutation burden, stimulator of interferon genes, immuno-negative genes, immune-positive genes, hyperprogression-related genes, genes related to DNA damage repair pathways, and subpopulations of peripheral blood mononuclear cells.

### Data collection and monitoring

2.11

The raw data of the study will be recorded and collected based on medical records or specific worksheets. All data will be cross-checked independently by two investigators. The researchers will retain all research records and original documents for 5 years after the study concludes. Security and environmental risk issues should be considered when preserving documents. The researchers will allow the relevant regulatory agencies direct access to all study-related documents, including participants’ medical records.

### Discontinuation/withdrawal/loss to follow-up

2.12

In the event of participant withdrawal or study termination, investigators will continue to collect data on AEs and survival status. For subjects who withdraw but remain eligible for follow-up, all procedures outlined in **Supplementary Table 1** will be performed. Participants who discontinue the study for reasons other than disease progression must undergo an imaging assessment upon treatment completion. If a scheduled follow-up visit is missed, the investigator will make attempts to contact the participant to reschedule the appointment and will document the outcome of these efforts.

### Statistical analysis

2.13

#### Sample size estimation

2.13.1

As reported in the literature (15), the mPFS of CRCLM subgroup in the control group is 1.8 months (regorafenib + nivolumab). The mPFS in the intervention group is estimated to be 3.7 months with a hazard ratio (HR) of 0.5. With a one-sided significance level of 0.05 (power of test of 80%), case enrollment of 18 months and follow-up of 12 months, and assuming a 5% dropout rate, a 1:1 enrollment ratio for the intervention and control groups will require sample sizes of 24 and 23 cases, respectively. In addition, a standardized treatment group with a sample size of 15 cases will be set up, totaling 62 cases. These three groups will be randomly enrolled in a 3:3:2 ratio. It is worth noting that the standardized treatment group is mainly used for descriptive comparisons and safety references, and is not included in the scope of the main hypothesis tests. The comparison between the intervention group and the control group is designated as the primary analysis.

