## Introduction

1

Early symptoms of colorectal cancer (CRC) are not obvious, and 25% of patients have distant metastasis at diagnosis, which cannot be cured by surgery alone (1). For metastatic CRC (mCRC), the progression-free survival (PFS) is about 10–12 months for first-line and 6 months for second-line therapy (2, 3). After failure of first- and second-line treatments, third-line and beyond therapies remain suboptimal. Currently, third-line therapies of mCRC recommended by major guidelines include fruquintinib, regorafenib, and trifluridine-tipiracil (TAS-102) with or without bevacizumab (4–6). Although extensive data for third-line treatment of mCRC have been published, the results show that the prognosis remains poor, with a median PFS (mPFS) of only 3.2-5.6 months (7–12). There is an urgent need to find novel therapies.

At present, immune checkpoint inhibitors (ICIs), such as programmed death-1 (PD-1) monoclonal antibodies, have achieved great success in clinical practice; however, for mCRC, the population benefiting from ICIs is still limited to about 5% of patients with high microsatellite instability (MSI-H) (13). The microsatellite stable (MSS) type, which accounts for 95% of mCRC, shows limited response to immunotherapy. Combination regimens are a major focus of immunotherapy research, and immunotherapy combined with targeted therapy holds great promise (14). Clinical studies have shown that targeted drugs combined with ICIs hold promising prospects for improving survival outcomes for MSS mCRC patients (15–17).

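### The 24 + 23 patients fall modestly short of the stated 80% power: the section's own inputs call for about 51 to 55 patients once 5% dropout is included

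*Protocol article*

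**What the plan says.** All the inputs stand in section 2.13.1 of the protocol article.

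- Control arm: "the mPFS of CRCLM subgroup in the control group is 1.8 months", taken from the literature.
- Intervention arm: "The mPFS in the intervention group is estimated to be 3.7 months with a hazard ratio (HR) of 0.5".
- Error rates: one-sided 0.05 and 80% power. Section 2.13.2 (Statistical analysis methods) agrees, "using a one-sided 0.05 hypothesis test of superiority".
- Timing: "case enrollment of 18 months and follow-up of 12 months".
- Loss: "assuming a 5% dropout rate".
- Result: "a 1:1 enrollment ratio for the intervention and control groups will require sample sizes of 24 and 23 cases, respectively", so 47 in the two arms.

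The section makes intervention versus control the primary analysis and leaves the 15-patient fruquintinib arm outside the hypothesis test. It states no number of events, formula or software for this calculation.

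**The concern.** For a time-to-event endpoint, power depends on the number of events, and each patient contributes at most one PFS event. At HR 0.5, one-sided 0.05 and 80% power, the usual formula asks for slightly more than 50 events. The two arms hold 47 patients, and the plan expects to lose 5% of them. So the printed sample size looked too small for its own inputs before any assumption about accrual or censoring.

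This is the only comparison for which the trial claims power. A non-significant result would be read as having had an 80% chance of detecting the target effect, and that chance is somewhat lower. The target is also stated in two forms that differ slightly (HR 0.5, and medians whose ratio is 0.486), so a reader cannot tell which effect the 80% refers to.

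**Working it through.** **Assumptions added to the stated inputs.** Exponential PFS, uniform accrual over 18 months, and 12 months of follow-up after the last enrolment.

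**1. Required events (Schoenfeld, 1:1).** Events = 4(z₀.₉₅ + z₀.₈₀)² / (ln HR)², with z₀.₉₅ = 1.645 and z₀.₈₀ = 0.842. The numerator is 4 × 2.4865² = 24.73.

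- Stated medians: HR = 1.8/3.7 = 0.486, ln HR = −0.7205. Events = 24.73/0.5192 = 47.6, so 48.
- HR exactly 0.5 (1.8 vs 3.6 months): ln HR = −0.6931. Events = 24.73/0.4805 = 51.5, so 52.

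**2. Probability of an observed event.** With λ = ln 2/median, P = 1 − (e^(−12λ) − e^(−30λ))/(18λ).

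- Median 1.8: 0.9986. Median 3.7: 0.9698. Median 3.6: 0.9723.
- Average over the two arms: 0.984 (1.8 vs 3.7) and 0.985 (1.8 vs 3.6).

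**3. Required patients, set against the plan's 47.**

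| | Events | Patients, no dropout | Patients, ÷ 0.95 |
|---|---|---|---|
| HR 0.486 | 47.6 | 47.6/0.984 = 48.4 | 50.9 → 51 |
| HR 0.5 | 51.5 | 51.5/0.985 = 52.2 | 55.0 → 55 |

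The plan's 47 is not reproduced. The nearest figures are those at HR 0.486 without dropout, and even 47.6 reaches 47 only by rounding down. Other standard methods ask for more:

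- Freedman: 52 or 56 events, and about 56 or 60 patients with dropout.
- Lakatos: 51.5 or 55.4 patients before dropout.
- Lachin–Foulkes: 54 or 58 patients before dropout.

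**4. What 24 + 23 patients deliver.** Expected events = 24 × 0.9698 + 23 × 0.9986 = 46.2 with no loss, and 46.2 × 0.95 = 43.9 with 5% lost outright. Power = Φ(√(D/4) × |ln HR| − 1.645), where D is the number of events.

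| Events D | HR 0.486 | HR 0.5 |
|---|---|---|
| 44 (5% lost) | 77.2% | 74.4% |
| 46 (almost none lost) | 78.8% | 76.0% |
| 47 (every patient has an event) | 79.5% | 76.8% |

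A log-rank simulation of 24 + 23 patients with 5% lost gave 75–76% at HR 0.486 and 72% at HR 0.5. With no loss it gave 77% and 74%.

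**5. Effect for which 80% does hold.** Solving for the HR, exp(−2 × 2.4865/√D) = 0.473 with 44 events and 0.480 with 46.

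**The case against.** **The gap is small.** This is fair. On the stated medians, Schoenfeld power is 1 to 3 points below 80%; at exactly HR 0.5 it is 4 to 6 points below. This is a phase II trial, and its Discussion calls for larger trials to validate findings in this field. The point therefore should be corrected, but it does not undermine the design.

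**HR 0.5 is just 0.486 rounded.** This is largely right. To one decimal the two agree, so the mismatch is not a separate error. It does set which end of the range applies: 51 patients if the medians are the design input, 55 if 0.5 is exact. Neither gives 47.

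**The 5% may have been meant differently.** If it is a loss rate per year, or over the whole 30 months, expected events rise to about 45.5–46.0. Power is then about 78–79% at HR 0.486 and 76% at HR 0.5. That narrows the gap without closing it. If follow-up instead means a fixed 12 months per patient, expected events fall to about 42–44.

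**A stronger reading that the document does not support.** The Introduction describes third-line outcomes "with a median PFS (mPFS) of only 3.2-5.6 months", and the 3.7-month target lies inside that range. A reader might infer that the 1.8-month control median is wrong and that true power is very low. But that range describes third-line metastatic colorectal cancer in general, whereas 1.8 months is for a liver-metastasis subgroup. The article itself argues that liver metastases worsen prognosis and blunt immunotherapy. Nothing in it gives 3.2 months or more as the median for this control arm. Taking the figure from regorafenib plus nivolumab is openly disclosed. It is a design judgement and not an arithmetic error.

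**Conclusion.** The stated sample size and power contradict the inputs printed with them. With the 5% dropout included, the inputs need 51 patients (HR 0.486) or 55 (HR 0.5), against 47 planned. With about 44 events, power is about 75–77% on the stated medians and 72–74% at HR 0.5. Even if all 47 patients had an event, Schoenfeld power would stay below 80% at either HR, and that last statement needs no assumption about accrual or censoring. The remaining figures rest on exponential PFS, uniform accrual and 5% lost outright.

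A reader might infer that the dropout allowance was simply forgotten. The closeness of 47 to 47.6 events and 48.4 patients points that way, but the article does not show its calculation, so this stays a suggestion.

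The shortfall is modest and should be fixed. It is no reason to doubt the trial's conduct or to enlarge it.

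**What to change.** Keep 24 + 23 patients and rewrite the calculation in section 2.13.1 so that its figures agree:

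- Use one effect throughout: either 1.8 vs 3.7 months with HR 0.486, or 1.8 vs 3.6 months with HR 0.5.
- State the expected number of PFS events, about 44 after 5% dropout.
- State the power this gives at one-sided 0.05: about 75–77% at HR 0.486 or about 72–74% at HR 0.5, with 80% reached only at HR about 0.47. Name the method, because Schoenfeld gives the upper and log-rank simulation the lower end of each range.

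The simulated figures treat progression times as exact. A simulation that moved every event to the next 12-weekly scan gave about 73% at HR 0.486 and 71% at HR 0.5, so the sponsor may prefer to quote the lower end.

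The cost is wording only, plus a slightly less favourable stated power. No patients are added, and the endpoint, alpha and analysis do not change.
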